# Evaluation of adherence monitoring system using evriMED with a differentiated response compared to standard of care among drug-sensitive TB patients in three provinces in South Africa: a protocol for a cluster randomised control trial

**DOI:** 10.1186/s13063-021-05337-y

**Published:** 2021-06-09

**Keywords:** Medication adherence, Tuberculosis, Medication monitor, Real-time medication monitoring

## Abstract

**Background:**

South Africa has achieved drug-susceptible TB (DS-TB) treatment success of only 77% among people with new and previously treated TB. Alternative approaches are required to improve medication adherence and treatment completion to limit transmission, TB relapse and the development of resistance. This study aims to implement and evaluate the use of adherence medication monitors (Wisepill evriMED 1000) with a differentiated response to patient care, among DS-TB patients in three provinces of South Africa.

**Methods:**

In total, 18 public health clinics across three provinces were selected. Clinics were randomised to intervention or standard of care clinics. In each clinic, approximately 145 DS-TB patients are being enrolled to reach a total of 2610. All patients have their daily adherence monitored using medication monitors. In the intervention arm, patients are receiving medication monitor reminders and differentiated care in response to adherence data. This weekly review of daily real-time monitoring will be undertaken from a central database. The differentiated care model includes automated SMS reminders with a missed dose, research staff-initiated phone call to the patient with a second or third missed dose, a home visit if four or more doses are missed, and motivational counselling if four or more doses are missed repeatedly. Fidelity of the intervention will be measured through process evaluation. Patients in control clinics will receive medication monitors for adherence tracking, standard of care TB education, and normal clinic follow-up procedures. The primary outcome is the proportion of patients by arm with >80% adherence, as measured by the medication monitor. The feasibility and acceptability of the intervention will be assessed by in-depth interviews with patients, stakeholders, and study staff. A cost effectiveness analysis of the intervention and standard of care clinics will be conducted.

**Significance:**

This trial will provide evidence for the use of an intervention, including medication monitors and differentiated care package, to improve adherence to TB treatment. Improved adherence should also improve TB treatment completion rates, thus reducing loss to follow-up rates, and TB relapse among people with TB. The intervention is intended to ultimately improve overall TB control and reduce TB transmission in South Africa.

**Trial registration:**

Pan African Trial Registry PACTR201902681157721. Registered on 11 February 2019.

**Supplementary Information:**

The online version contains supplementary material available at 10.1186/s13063-021-05337-y.

## Introduction

Globally, an estimated 10 million people with TB were identified with new and previously treated tuberculosis (TB) in 2018 [1]. Of the 6.4 million people with TB, who started on treatment in 2017, treatment success was reported in 85% [1]. South Africa reported treatment success rates of 77% among all people with new and previously treated TB as well as 75% among HIV-positive people with TB [1]. Poor medication adherence contributes to lower treatment completion among people with TB [2]. Poor medication adherence also contributes to an increased rate of TB relapse [3].

Systematic reviews show that the traditional approach to facility-based directly observed treatment (DOT) does not improve treatment completion, microbiological cure, disease relapse rates, and rates of acquired drug resistance when compared to self-administered therapy [4–6]. Facility-based DOT is time-consuming, is highly resource intensive, and creates barriers to retention in care and treatment completion. It is also inconvenient to people living with TB and results in loss of income and employment [7, 8]. Alternative and innovative approaches are required to improve medication adherence and treatment completion to limit transmission, TB relapse, and the development of drug-resistance.

A number of digital health adherence technologies have been explored recently including the electronic medication monitor (as in this study), the 99-DOTs (a cardboard sleeve which requires patients to send a short message services [SMS] or make a missed call after taking a dose) [9], and video-supported treatment [10] (smart phone based technology using video to record medication intake). A cluster randomised trial of 4500 TB patients in rural and urban China showed improved medication adherence in patients randomised to the medication monitor compared to SMS messaging or the standard of care [11]. The medication monitor was well accepted by patients and providers [12]. A differentiated care approach, one of the pillars of the End-TB strategy, defined as a client-centred approach that simplifies and adapts services along the care cascade, may better serve the needs of patients and reduce the burden on the health system and has the potential to improve medication adherence [13]. A further study to evaluate the use of medication monitor, this time with real-time reporting and with differentiated care, is being conducted in China [14]. Electronic medication monitors have not been formally evaluated in drug-susceptible TB (DS-TB) patients in South Africa. The use of these electronic monitors could assist the country in reaching the global TB plan target of 90% successfully completing their treatment. Monitoring of the adherence data will assist in identifying who needs more support under a differentiated model thereby directing scarce resources to them. In this trial, we will evaluate whether implementation of a medication monitor (smart pill box; Wisepill evriMED 1000 device), coupled with daily monitoring and differentiated care, is able to improve adherence and reduce poor outcomes in patients with DS-TB treatment.

## Methods

The study protocol has been reported in accordance with the Standard Protocol Items: Recommendation for Clinical Interventional Trials (SPIRIT) guidelines (additional file 1 for details).

### Study design and setting

The trial is parallel group, cluster-randomised taking place in six clinics in each of three provinces in South Africa: Gauteng (Ekurhuleni district), Western Cape (Klipfontein and Mitchell’s Plain districts), and Kwa-Zulu Natal (eThekwini district). The study is evaluating if the intervention is superior to the control treatment. Clusters were defined as public health clinics with at least 200 TB registrations in 2017. Adult HIV prevalence in the general population is 18.2% in Kwa-Zulu Natal, 12.5% in Gauteng, and 8.9% in Western Cape province [15]. Prior to randomisation, we considered urban or rural location of clinic, total number of patients starting TB treatment per month, and treatment outcomes in the last 12 months. Clusters were randomised 1:1 to intervention or standard of care arm using restriction to ensure that each province has at least one intervention and one standard of care clinic [16]. Randomisation was conducted by a computer programme (Stata) which generated all possible randomisations (48,620). Restrictions were applied to eliminate randomisations for which facilities in the two groups were not balanced by province (0–1 or 5–6 facilities from each province per arm) which left 35,000 possible options. Ten thousand of the randomisations were randomly selected for convenience and listed in an Excel spreadsheet, labelled as 0000–9999. Clinic/DOH representatives present at the randomisation meeting chose 4 golf balls (each numbered 0,1,… 9) to select a randomisation option. Unfortunately, following the randomisation though before participant enrolment had started, two clinics, from each arm (same province), had to withdraw due to ongoing TB studies. These were replaced by two clinics in the same province and were allocated to the intervention and control arm at random.

### Study population and eligibility criteria

The study is recruiting all adults aged ≥18 years and children aged 2–17 years with clinically or microbiologically diagnosed DS-TB. The inclusion criteria include initiating TB treatment within the last 14 days, adults and caregivers of children who are willing and able to provide informed consent, and children aged 7–17 years old who are willing and able to provide informed assent. Patients need to be willing to use the medication monitor; agree to be followed-up with text messaging, phone calls, and home visits; live within the study catchment area; and be willing to inform the study team of any change of address during the treatment as well as follow-up period. We expect to enrol approximately 2610 DS-TB patients and follow them up for 18 months post enrolment. The study started enrolment in May 2019 and will complete follow-up in December 2021. This manuscript could not be submitted for consideration before enrolment commenced as the methodology had to piloted and refined during the early phases of the enrolment period.

### Description of study arms and procedures

#### Intervention clinics

Enrolled patients receive the differentiated care adherence package. This includes standard patient education and provision of medication monitor programmed to alert patients (using sound and a light on the box) on a daily basis as a reminder to take their medication (Table 1). Patients are educated on how to use the medication monitor by the study team. The medication monitor transmits a daily signal to the Wisepill system (system), referred to as heartbeat, to indicate that it is working properly. There are also additional reminders for monthly dispensing visits and the device uploads data in real-time to a central database that allows for weekly review by research staff. Weekly automated reports are generated from the system that lists patients who had missed any doses and those whose devices are not sending a signal correctly. A step-wise approach to missed doses is then implemented that includes phone calls, home visits, and motivational counselling for those who consistently miss medication doses (Table 2). Automated SMS reminders are sent to any patient in the intervention with a missed dose. A second or third missed dose in a week triggers a research staff-initiated phone call to the patient, and four or more missed doses in a week trigger a home visit. Phone calls and home visits are scripted. Should four or more doses be repeatedly missed, additional adherence measures such as motivational counselling is done. When participants visit the clinic for their usual dispensing visit, the research staff shows the participant their own data and discusses their medication adherence history.

**Table 1 Tab1:** Description of scheduled study visits

***Study Visit*** ***Month (M) and*** ***Day (D)***	***D0*** ***(Enrolment)***	M1	M2	M3	M4	M5	M6	M9	M12	M15	M18
Informed consent	**√**										
Eligibility criteria verified	**√**										
Of those eligible:											
Locator information	**√**	**√**	**√**	**√**	**√**	**√**	**√**	**√**	**√**	**√**	**√**
Brief medical history	**√**										
Risk assessment for TB	**√**										
Economics questions	**√**										
Stigma scale	**√**						**√**				**√**
Facility dispensed treatment	**√**	**√**	**√**	**√**	**√**	**√**					
Education on the medication monitor and monitor provided to patient	**√**										
Medication monitor configured to have visual and audio reminders—intervention arm only	**√**										
Participants’ experience using medication monitor and adherence discussion for intervention—intervention arm only		**√**	**√**	**√**	**√**	**√**	**√**				
Social harm							**√**		**(√*)**		
Pre-treatment, two and five months routine specimens abstracted from record							**√**				
Treatment completion history abstracted from routine records							**√**				
TB Symptom screen**								**√**	**√**	**√**	**√**
Research clinic visit								**√**	**√**	**√**	**√**
Sputum culture and GXP	**√**^**(**^*****^**)**^						**√**	**(√)**	**(√)**	**(√)**	**√**

*GXP* Gene Xpert MTB/Rif

(*) collect culture for those who were diagnosed via chest radiograph or clinically or have negative GXP result; **TB investigations performed if participant is symptomatic for TB; (√) sputum collected for culture and GXP if TB symptoms are reported at that visit; (√*) only done if social harm case report form was not completed at month 6

**Table 2 Tab2:** Description of the differentiated care in the intervention arm

Weekly adherence	Weekly doses missed	Intervention
85%	1	Same day SMS reminder (automated)
45–84 %	2 or 3	Voice call by research staff
<45%	4 or more	Home visit and/or clinic visit
	Greater than 1 week with 4 or more missed doses	Recall for other adherence measures, e.g. motivational counselling.

#### Standard of care clinics

Enrolled patients are provided with a return date for collection of repeat medication in 30 days. Patients are also provided with the medication monitor and educated on its use by the study team (Table 1). The medication monitor records data on box opening and is not configured to have visual or audio reminders for intakes or refills. The medication monitor transmits a daily “heartbeat” signal to the system to indicate that it is working properly. In contrast to the intervention clinic patients, data collected on the system is not reviewed during follow-up study visits. Patients receive counselling regarding their TB treatment as per standard of care only. Neither the research staff nor the patient accesses the medication monitor information at follow-up study visits.

#### Follow-up

Follow-up of all patients in intervention and standard of care arms continues every 3 months until 12 months after completion of treatment (approximately 18 months after enrolment) (Table 1). Patients who die, declared as loss to follow-up during treatment by facility staff, or move out of our study area will be withdrawn from study. At each follow-up visit, TB symptom screening will be performed and, if required additional investigations such as sputum tests, will also be conducted. Patients are reimbursed ZAR 50 for travel costs for each visit. All patients are requested to provide sputum specimens for culture testing at 6 months from enrolment and 12 months post TB treatment completion (18 months from enrolment).

### Qualitative evaluation

The feasibility and acceptability of the intervention will be assessed by conducting at least 60 in-depth interviews with patients who received the intervention, and at least six stakeholders and study staff who implemented the intervention. Patient interviews will be done post enrolment across varied follow-up times to allow for variation regarding the use of medication monitors. They will also be selected according to their gender, age and how adherent they are according to the weekly analysed adherence data (adherence category). These patients will be reimbursed R150 for their time. For feasibility of the intervention, we will explore the following: how easy it was to use the medication monitors, concerns about inadvertent disclosure of TB status with having a medication monitor for medication, and how useful patients found the SMS reminders, calls and home visits. Key stakeholders at provincial and district level will be interviewed to understand the motivators and challenges to integrating this model of care into the current health system and how the use of this technology could influence policy change. For acceptability, we will explore appropriateness of the intervention, issues encountered, and perceptions of benefit from both patients and providers.

### Economics evaluation

The cost-effectiveness analysis of the intervention will entail estimating all direct and indirect costs from the intervention and standard of care clinics. Costing will be based on a societal perspective. All costs related to the resources utilised in delivering the intervention such as personnel, equipment, supplies, and training will be gathered using a bottom-up costing approach. Personnel costs associated with time spent conducting their daily activities will be acquired using a survey and time and motion methods and timesheets. Time spent on voice calls to patients will be estimated using itemised billing records from the service provider. Patient costs will be estimated using a questionnaire at enrolment, 2 and 6 month’s visits, and compared in both trial arms to identify patient cost drivers. We will calculate the incremental cost-effectiveness ratio for the clusters per treatment arm.

### Ethics approval

The study has ethical approval from the University of Witwatersrand (Ref 180705) and the University of Cape Town (Ref 452/2018), as well as, from the London School of Hygiene & Tropical Medicine (Ref 16107). It also has approval from the health management of the three Provincial Offices, as well as City of Cape Town, eThekwini and Ekurhuleni district research committees. The study has a Trial Steering Committee that meets biannually to discuss study progress. The trial steering committee is comprised of six members and these are the following: PI of the study, Western Cape regional PI, National Department of Health representative, South African-based TB expert, and two internationally based TB experts. The steering committee is responsible for providing expert oversight of the trial, monitoring recruitment as well as follow-up rates and reviewing strategies from the investigators to deal with problems, providing recommendations as to the future continuation of the trial, reviewing regular data reports of the trial progress, and lastly approving external or early internal requests for release of data or subsets of data or samples including clinical data and stored biological samples. Written, informed consent is being sought from all potential participants by study staff (research assistant) before taking part in the study. Assent is also being obtained from participants aged 7–17 years.

### Trial outcomes

The primary study endpoint is medication adherence which will be measured as the proportion of patients by arm with >80% adherence, as measured by the medication monitor. For those lost to follow-up during treatment, we will assume no drug intake (100% non-adherence) for the period from the date of being lost to follow-up to the date of scheduled treatment completion. Secondary endpoints will be successful outcome at the end of treatment and unfavourable outcomes at 18 months post enrolment. Treatment success will be measured as the proportion of patients by arm that either have a documented cure or treatment completion by 210 days following commencement of TB treatment. A TB culture will be performed at the end of treatment to confirm response to treatment. TB recurrence will be determined through incident TB cases in the year following completion of DS-TB treatment. Unfavourable outcome at 18 months after enrolment will include on-treatment lost to follow up, death, treatment failure, and treatment recurrence. Fidelity of the intervention will be measured by reporting on percentage of patients who were supposed to receive an SMS or phone call who did and percentage of patients who received counselling when required. We will also report on percentage of boxes with failures. We will also report on percentage of patients withdrawing from study due to refusal of using digital adherence technology.

Qualitative outcomes will be on appropriateness and perceptions of patients as well as providers involved with the implementation of the intervention. We will also report on reaction to use of the medication monitor as well as the suitability of this medication monitor to participant living conditions, the motivators of using the medication monitor to take treatment, and challenges to integrating the differentiated model of care into the current health system. We will further explore differences across patients by age, category of adherence, and location.

Economic outcomes will be based on cost per person with >80% adherence to DS-TB treatment, cost per person with TB who successfully completed DS-TB treatment, proportion experiencing catastrophic costs, and cost drivers and incremental cost-effectiveness ratio.

### Study outcomes’ definitions

Treatment completed is defined as patient who has completed their treatment without evidence of failure but without any record of a negative smear or culture result in the last month of treatment or any time in previous occasion.

Cured is defined as pulmonary TB patient with a positive smear, Xpert MTB/Rif or culture result (bacteriologically confirmed TB) at the beginning of treatment who has a negative smear microscopy or culture result at the last month of treatment.

Lost to follow-up is defined as a patient whose treatment has been interrupted for more than 2 months.

Treatment failed is defined as a patient whose sputum smear or culture is positive at month 5 or later during treatment.

TB recurrence is defined as a patient with a positive culture result at any time during the 12 months follow-up period post treatment completion.

Unfavourable outcome at 18 months post enrolment is defined as treatment failure, lost to follow-up and death during treatment, and recurrence after end of treatment.

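### Taken literally, the definitions of cured and treatment completed leave some patients who finish treatment without failure in neither category, so the secondary treatment-success endpoint does not count them

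*Protocol article*

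**What the plan says.** Under Trial outcomes, treatment success, a secondary endpoint, is the "proportion of patients by arm that either have a documented cure or treatment completion by 210 days" from the start of treatment. The two components are defined under Study outcomes' definitions.

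- **Cured.** The baseline condition reads: "Cured is defined as pulmonary TB patient with a positive smear, Xpert MTB/Rif or culture result (bacteriologically confirmed TB) at the beginning of treatment". The end condition limits this to a patient "who has a negative smear microscopy or culture result at the last month of treatment".
- **Treatment completed.** The patient has finished "without evidence of failure but without any record of a negative smear or culture result in the last month of treatment or any time"; the sentence goes on to make clear that this means any earlier occasion.

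The trial enrols patients with "clinically or microbiologically diagnosed DS-TB", and the eligibility criteria do not exclude extrapulmonary disease. The footnote to Table 1 tells staff, at enrolment, to "collect culture for those who were diagnosed via chest radiograph or clinically or have negative GXP result". Table 1 also has routine pre-treatment, month-2 and month-5 results abstracted from the record. Under Follow-up, "All patients are requested to provide sputum specimens for culture testing at 6 months from enrolment".

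Data management and analyses describes the secondary variable only as a binary indicator of whether six months of treatment were successfully completed. It states no sputum condition.

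**The concern.** Two categories that together make up success should cover everyone who finishes treatment without failing. These do not. *Cured* excludes patients without bacteriological confirmation at baseline, and *treatment completed* excludes anyone with a negative result on record. A patient who is excluded by both has no success category.

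The trial's own procedures produce such patients. A clinically diagnosed patient has a culture taken at enrolment. If it is negative, the patient already has an earlier negative result and can be neither cured nor completed, however treatment goes.

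The rule also runs backwards: an unconfirmed completer with no sputum result is a success, while the same patient with a documented negative culture is not. The unfavourable outcome is built from failure, loss to follow-up, death and recurrence, so being left out of success does not make these patients unfavourable.

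At stake are an endpoint with its own power statement and, if it uses the same definition, the economic outcome of cost per person successfully completing treatment.

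**Working it through.** **Step 1. Classify every type of completer.** Take patients who finish without failure and cross three facts: confirmed pulmonary TB at baseline or not; last-month result negative or absent; earlier negative on record or not. A positive smear or culture at month 5 or later is failure, so a last-month positive does not arise here.

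| Baseline | Last month | Earlier negative | Cured | Completed | Success |
|---|---|---|---|---|---|
| Confirmed pulmonary | negative | yes | yes | no | yes |
| Confirmed pulmonary | negative | no | yes | no | yes |
| Confirmed pulmonary | none | yes | no | no | **no** |
| Confirmed pulmonary | none | no | no | yes | yes |
| Unconfirmed or extrapulmonary | negative | yes | no | no | **no** |
| Unconfirmed or extrapulmonary | negative | no | no | no | **no** |
| Unconfirmed or extrapulmonary | none | yes | no | no | **no** |
| Unconfirmed or extrapulmonary | none | no | no | yes | yes |

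Four of the eight types are left out. This counts types, not patients.

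**Step 2. Try a looser reading.** Suppose *treatment completed* means lacking at least one of the two results (last month, earlier). Three of the four types then become completed. The unconfirmed or extrapulmonary patient who is negative both earlier and in the last month is still left out.

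**Step 3. Reproduce the stated power.** Inputs from Sample size considerations: m = 145 per cluster (harmonic mean), 9 clusters per arm, two-sided 5%, p0 = 0.80, p1 = 0.90, k = 0.06. With the unmatched cluster formula:

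V = [p0(1−p0) + p1(1−p1)]/m + k²(p0² + p1²) = 0.25/145 + 0.0036 × 1.45 = 0.001724 + 0.005220 = 0.006944

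c = 1 + (1.960 + 1.282)² × V/(p1−p0)² = 1 + 10.51 × 0.006944/0.01 = 8.30, rounded up to 9.

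Power at 9 clusters = Φ(√[8 × 0.01/0.006944] − 1.96) = Φ(1.43) = 92%. A t test with 16 df also gives 92%, on either the proportion or the log scale. The stated 9 clusters and 90% power are reproduced.

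**Step 4. Size of the gap.** Let g be the share of true successes left out. The protocol does not give g, so it is an assumption, taken as equal in both arms with k held at 0.06. Recorded success is 0.80(1−g) v 0.90(1−g).

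| g | Recorded success | Difference | Ratio | Power at 9 per arm |
|---|---|---|---|---|
| 0 | 80% v 90% | 10 points | 1.125 | 92% |
| 10% | 72% v 81% | 9 points | 1.125 | 88% |
| 20% | 64% v 72% | 8 points | 1.125 | 81% |
| 30% | 56% v 63% | 7 points | 1.125 | 73% |

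For example, at g = 30%: V = 0.4795/145 + 0.0036 × 0.7105 = 0.005865, and Φ(√[8 × 0.0049/0.005865] − 1.96) = Φ(0.63) = 73%.

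**Step 5. Direction of any differential error.** Suppose one arm obtains more end-of-treatment specimens.

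- An unconfirmed completer with no earlier negative moves from completed into the gap. This counts against that arm.
- A confirmed pulmonary completer with an earlier negative moves from the gap to cured. This counts for that arm.
- An unconfirmed completer who already has a negative baseline culture is in the gap either way.

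The first two effects oppose each other, and the protocol gives no numbers with which to weigh them.

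**The case against.** The strongest reply is that nobody would apply the definitions literally. The wording of *treatment completed* is awkward, Table 1 has treatment completion history abstracted from routine records, success is described as documented, and the analysis section speaks only of having successfully completed six months. The endpoint may therefore follow the recorded programme outcome, with coding settled in the promised analysis plan. This makes literal application uncertain, and that part stands. It does not remove the fault. The article does not leave the definition to another document; it states one, and the analysis section gives no rule for the patients who fall outside it. The looser reading in step 2 narrows the gap without closing it.

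Objections to stronger readings succeed:

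- A reader might set the fall in recorded success (8 points at g = 10%, 24 at g = 30%, from 80%) against the 10-point effect the trial is powered for. These are different quantities. The fall is in the level; with equal shares the difference between arms shrinks only to 9 or 7 points. The ratio is unchanged, and the ratio is what the log-proportion comparison described for adherence would estimate if it is also used here.
- A reader might infer bias against the intervention because better retention yields more negative results. Step 5 shows that the two affected groups work in opposite directions.
- A reader might conclude that the best-documented responders are lost, or everyone without a last-month result. Confirmed patients with a last-month negative are cured, and a completer with no negative at any time is completed.

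**Conclusion.** The definitions are wrong as written for one secondary endpoint. Unconfirmed or extrapulmonary completers with any negative smear or culture on record, and confirmed pulmonary completers with an earlier negative but no last-month negative, are neither successes nor unfavourable outcomes. The trial's sampling schedule makes such patients expected.

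The size is unknown. If 10% to 30% of successes are affected, equally in both arms and with k = 0.06, power falls from about 92% to about 88% or 73%, and recorded success is understated in both arms. Differential bias is possible if the arms differ in specimen collection or in the mix of confirmed patients, but its direction cannot be determined from the protocol. The primary adherence endpoint and the 18-month unfavourable outcome do not use these two categories and are not affected.

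**What to change.** Before analysis, define *treatment completed* for this endpoint as having finished treatment without evidence of failure and not meeting the definition of cured, whether or not negative smear or culture results are on record. All eight types in step 1 then count as successes, and each falls in exactly one category. State that the binary variable in Data management and analyses is built from these two categories within the 210-day limit, and that the cost per successfully treated person uses the same variable.

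The cost is one definition sentence and one cross-reference. The data are already being collected, and nothing changes for sites or patients.
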